**Prophylactic Oxytocin IV Infusion vs. IM Injection in the Third Stage of Labor**

**Research Objectives**

Primary objectives

- To evaluate whether 10 IU prophylactic oxytocin administered in the third stage of labor via IV infusion results in a lower mean blood loss compared to IM injection.
- To also compare the effect of IV infusion and IM oxytocin administration on the proportion of women who experience blood loss  500 ml.

Secondary objectives

- To compare the effect of IV infusion and IM oxytocin administration on the proportion of women who experience blood loss  1000 ml, side effects, adverse events and change in hemoglobin pre- to post-delivery.
- To determine the relationship that exists between changes postpartum in shock index and the severity of bleeding and other PPH outcomes.

This study will provide answers to the following research questions:

1. Is administration of oxytocin by IV infusion more effective than IM administration of oxytocin at reducing post-partum blood loss when provided as part of AMTSL?
2. Is the mean difference between pre-delivery and post-delivery hemoglobin levels less with IV infusion than with IM administration?
3. Do the side effect profiles differ between IV infusion and IM oxytocin administration?

# Is shock index a potential useful indicator for evaluating the severity of postpartum bleeding during the first hour postpartum and initating clincial intervention for PPH management?

**Outcome Measures**

Primary outcome measures:

- Mean blood loss (ml)
- Proportion of women who bleed  500 ml

Secondary outcome measures:

- Proportion of women who bleed  1000 ml
- Change in hemoglobin from pre-delivery to postpartum
- Time to placental delivery
- Administration of additional oxytocin, other uterotonics, or other interventions such as blood transfusion and hysterectomy
- Side effects 1 hour postpartum
- Measurements of blood pressure and pulse during the first hour postpartum.

**Description of Study Site**

*Corrientes, Argentina:* El Hospital J.R. Vidal is a public, tertiary level institution situated in the capital of Corrientes. In 2012, a total of 3,080 deliveries were atended at this instituion. Approximately, 30% were cesarean deliveries. Oxytocin is available and used routinely during the third stage of labor.

**Explanation of Sample Size**

The primary outcomes of the study are (1) mean blood loss and (2) the proportion of women with PPH (defined as ≥500 ml).

This study is designed to detect a 50 ml difference in mean blood loss after provision of oxytocin prophylaxis via IV infusion and IM injection. In the published literature, a 50 ml difference has been shown to translate to approximately a 50% reduction in PPH rates (≥500 ml) . Based on the assumption that oxytocin prophylaxis IV will yield a mean blood loss of 275 (SD175)we estimate that a total of 257 women would be required in this superiority trial to detect a 50 ml difference in mean blood loss between the two groups with 80% power at a significance level of 0.05.

A prior study of PPH conducted at Hospital Vida had documented a rate of blood loss ≥500 ml of 18%, among women who received prophylactic oxytocin (10 IU) in the third stage of labor and with blood loss objectively assessed using a calibrated receptacle. Based on the assumption that oxytocin prophylaxis IV will yield a clinically meaningful reduction of at least 50% in the proportion of women with blood loss ≥500 ml , we calculate that a total of 442 women (vaginal deliveries) (221 per group) are required in this superiority trial to compare a 18% PPH rate following IM injection and a 9% PPH rate following IV infusion with 80% power at a significance level of 0.05. The sample size will be increased by 10% to account for any loss to follow up or missing blood loss readings for assessment of both primary outcomes. Thus, **a total sample size of 486 (243 per arm) is required** for the study in Ecuador. This sample size will be sufficient to detect a 50 ml mean difference in blood loss between study groups.

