***Analysis and Dissemination of Results***

Bivariate analyses will be conducted, stratified by study arm. Unadjusted and adjusted logistic regression will be conducted respectively for categorical and continuous dependent variables.

To compare the two study arms (oxytocin IM vs. oxytocin infusion), the main analyses will include:

- Mean postpartum blood loss (primary outcome)
- % of women with blood loss ≥500 ml (primary outcome)
- Median postpartum blood loss and interquartile range
- % of women with blood loss ≥1000 ml,
- Mean change in Hb measured pre- to post-delivery
- % of women with postpartum Hb drops of 2 g/dl or greater
- % of women with prolonged third stage of labor
- % of women who received additional oxytocics or other interventions to manage bleeding
- % of women who experienced side effects

We will register use of any other AMTSL components, such as controlled cord traction, uterine massage, etc. that are used.

In order to assess the relationship between shock index and severity of bleeding, we will correlate shock index values, heart rate, and blood pressure measures to blood loss levels that will be recorded at 15, 30, 45, and 60 minutes following delivery. Absolute values and measured changes in these values during the first hour following delivery will be analyzed. We will also explore associations between these clinical signs/symptoms with other PPH outcomes, including provision of additional interventions to control bleeding, blood transfusion, and other severe outcomes.

Data will be owned by Gynuity Health Projects. The principal investigators and study coordinators will work together to analyze the results of the study and prepare at least one manuscript for submission to one or more relevant peer-reviewed journals. In addition, members of the study team will present the results of the study at conferences and meetings where appropriate. All principal investigators will be named along with key Gynuity staff as authors of any publications or presentations describing results from the study.

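### Two primary outcomes are each sized at the full 0.05 with no rule for combining them; if either one suffices, the two-sided error is about 8%

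*Protocol*

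**What the plan says.** Research Objectives, Outcome Measures, Explanation of Sample Size, and Analysis and Dissemination of Results all treat two outcomes as primary. The sample-size section says: "The primary outcomes of the study are (1) mean blood loss and (2) the proportion of women with PPH", with PPH defined there as at least 500 ml.

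Each outcome has its own calculation at the full level:
- Mean blood loss is to "detect a 50 ml difference in mean blood loss between the two groups with 80% power at a significance level of 0.05".
- For PPH, the comparison is 18% after IM against "a 9% PPH rate following IV infusion with 80% power at a significance level of 0.05", giving 221 per group. This outcome sets the trial size (442, raised to 486).

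The two calculations are linked by the statement that "a 50 ml difference has been shown to translate to approximately a 50% reduction in PPH rates".

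Research question 1 asks a single question, whether IV infusion reduces blood loss more than IM. The protocol does not say which of the two outcomes answers it. It gives no testing order, alpha split or success rule, and it does not state sidedness or the correlation between the outcomes.

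**The concern.** Two tests at 0.05 feed one efficacy question. If one significant result is enough, the 0.05 quoted for each calculation is not the error rate of the overall conclusion. If both are needed, 80% power for each outcome is not 80% power for the trial. If one outcome is significant and the other is not, the protocol offers no agreed reading, and a rule chosen after the data are seen would not be confirmatory.

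**Working it through.** **1. Is the 0.05 spent in full on PPH?** Inputs are 18% and 9%, alpha 0.05 and power 80% (Explanation of Sample Size). The unpooled two-sided formula gives

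n = (1.96 + 0.8416)² × (0.18×0.82 + 0.09×0.91) / 0.09² = 7.849 × 0.2295 / 0.0081 = 222.4 per arm.

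The pooled version gives 226, and the protocol states 221. A one-sided test would need 178 and a split to 0.025 would need 273. So 221 corresponds to an unsplit two-sided 0.05.

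**2. Power for the mean at 221 per arm**, difference 50 ml, SD 175 in both arms:

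50 / (175 × √(2/221)) = 3.00; Φ(3.00 − 1.96) ≈ 85%.

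(The stated total of 257 for this outcome does not come out of the usual formula: 2 × 7.849 × 175²/50² = 192.3, so 193 per arm. That is a separate matter. The PPH-driven 442 covers 386.)

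**3. Error if either outcome suffices.** With independent tests it is 1 − 0.95² = 9.75%. The outcomes are not independent, because at least 500 ml is a cut of the same measurement. Bivariate normal results for two two-sided 0.05 tests:

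| Correlation of test statistics | Chance of at least one significant |
|---|---|
| 0 | 9.75% |
| 0.64 | 8.6% |
| 0.75 | 8.1% |
| 0.90 | 7.0% |
| 0.95 | 6.5% |

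The correlation is not in the documents. Null simulations at 221 per arm with SD 175 (t-test on the mean, pooled z-test on at least 500 ml) gave correlations of 0.72–0.76 and error of 7.8–8.3% for lognormal and gamma shapes with means of 275–325 ml. Normal shapes gave about 8.6–9%. Counting only false results that favour IV, the figure is about 4%, against 2.5% for a single two-sided test.

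**4. Error if both are required.** It cannot exceed the level of either test, so it is at most 5%. When neither outcome differs, both are falsely significant in about 2% of trials.

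**5. Power under the 50 ml effect** (325 vs 275 ml, 221 per arm). The protocol gives SD 175 beside the IV mean only. Two assumptions are shown for IM: SD 175, and SD proportional to the mean, 175 × 325/275 = 207. In a normal shape with SD 175, the IV rate is P(Z ≥ 225/175) = 9.9% and the IM rate is P(Z ≥ 175/175) = 15.9%, a 37% reduction. With IM SD 207, the IM rate is P(Z ≥ 175/207) = 19.9%, a 50% reduction.

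| IM SD | Shape | ≥500 ml, IM vs IV | Power, mean | Power, PPH | Both | PPH alone |
|---|---|---|---|---|---|---|
| 175 | lognormal | 13.4% vs 9.4% | 85% | 27% | 26% | 0.2% |
| 175 | gamma | 15.0% vs 10.6% | 85% | 28% | 28% | 0.2% |
| 175 | normal | 15.9% vs 9.9% | 85% | 46% | 45% | 1.4% |
| 207 | lognormal | 15.2% vs 9.4% | 78% | 45% | 44% | 1.4% |
| 207 | gamma | 17.5% vs 10.6% | 78% | 54% | 52% | 2% |
| 207 | normal | 19.9% vs 9.9% | 78% | 84% | 71% | 13% |

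The column for both equals PPH power minus PPH alone. Repeat runs move the entries by about one percentage point.

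**The case against.** **The protocol never says that either outcome alone would do.** This stands. A reader might infer that the trial's false-positive rate simply is 8%. The text does not support that: it is silent on the rule, and a both-required rule fits the wording equally well and has no inflation. The 8% is conditional. It also counts errors in both directions, and the error that matters for the stated objective is about 4%.

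**Testing order and alpha allocation are often left to a statistical analysis plan, and only the protocol is at hand.** This stands in part. A plan could still supply the rule. But the protocol has already fixed two primary outcomes, the full 0.05 for each, and the N. Those choices limit what a later plan can do: an either-rule exceeds 0.05, a split needs more women than planned, and a both-rule falls short of 80% power under the protocol's own 50 ml effect.

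**The low PPH power depends on the IM SD.** This stands. A reader might infer that 50 ml cannot give a 50% reduction in PPH, or that a significant mean with a non-significant PPH is the likeliest positive result. Both readings need SD 175 in the IM arm, which the protocol does not state. With IM SD 207 the reduction is about 38–50%, and in the normal shape PPH has more power than the mean. The protocol also attributes the link to literature not available here.

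**A fixed sequence is only one valid rule, and the order in which objectives are listed is not a hierarchy.** This also stands. PPH is the outcome that sets the sample size, so placing it second has a price that should be stated.

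**Conclusion.** The point holds as a conditional one. Two primary outcomes each take the full 0.05 and the protocol gives no rule for combining them.

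- **Either suffices:** two-sided familywise error is about 8% (about 7.8–9% over the shapes tried), or about 4% rather than 2.5% for a false claim favouring IV. This rests on an assumed distribution and correlation.
- **Both required:** error is at most 5%. Joint power under 325 vs 275 ml is about 26–45% with SD 175 in both arms, and about 44–71% with IM SD 207.

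Neither reading delivers both the stated 0.05 and the stated 80% across these scenarios. The gap can be closed within the planned N.

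**What to change.** Before unblinding, state a rule that holds error at 0.05. An example that keeps the planned N is a fixed sequence in the listed order. Test mean blood loss at two-sided 0.05. Test blood loss of at least 500 ml at two-sided 0.05 only if the first is significant. Otherwise report PPH as an estimate with its confidence interval and no confirmatory claim.

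This takes one or two sentences and no extra women. The price is a lost PPH claim whenever only PPH is significant: about 0.2–2% of trials for skewed blood loss, and up to about 13% for a normal shape with IM SD 207.

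The alternatives are valid but cost more:
- **Split alpha (0.025 each):** PPH needs 273 per arm, 546 in total, or about 601–607 after the 10% allowance. At 221 per arm, power is 70% for PPH (18% vs 9%) and 78% for the mean (50 ml, SD 175).
- **Both required:** no alpha cost, but the joint power given in the verdict.

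In Explanation of Sample Size, add the PPH power under the 50 ml scenario beside the 18% vs 9% calculation, with its assumptions: about 26–46% if the SD is 175 in both arms, and about 45–85% if the IM SD is about 207. State the SD assumed for the IM arm.

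### The 257 women stated for the mean blood loss outcome do not follow from their own inputs, which need 386 in total (two-sided); the enrolment target of 486 is unaffected

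*Protocol*

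**What the plan says.** All the relevant text is in the protocol section Explanation of Sample Size.

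- The first of the two primary outcomes is mean blood loss, and the section opens its case with it: "This study is designed to detect a 50 ml difference in mean blood loss".
- The inputs are given as "oxytocin prophylaxis IV will yield a mean blood loss of 275 (SD175)we estimate", followed by the result: "a total of 257 women would be required in this superiority trial to detect a 50 ml difference in mean blood loss".
- The error rates attached to that result are "with 80% power at a significance level of 0.05". Whether the test is one-sided or two-sided is not stated.
- A separate calculation for the second primary outcome (18% against 9% of women losing at least 500 ml) gives 442 women, 221 per group, again at 80% power and 0.05.
- The larger figure is then inflated: "The sample size will be increased by 10% to account for any loss to follow up or missing blood loss readings". This leads to "a total sample size of 486 (243 per arm) is required".
- The section closes by returning to the mean: "This sample size will be sufficient to detect a 50 ml mean difference in blood loss between study groups".

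**The concern.** The section supplies every input for a standard two-group comparison of means, so the stated total can be checked directly. It fails the check, and it errs on the low side. The figure is the only sample size calculated specifically for the outcome listed first. A reader who takes it at face value would conclude that the mean comparison reaches 80% power at 257/486 = 53% of planned enrolment. On the protocol's inputs, the power at that point would be well short of 80%.

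**Working it through.** **Inputs, all from Explanation of Sample Size.** Difference 50 ml; SD 175 ml; power 80%; significance level 0.05; equal allocation (243 per arm). The SD is given only alongside the IV mean of 275 ml, so I assume it applies to both arms. Sidedness is not stated, so both cases are shown.

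**1. Sample size from the stated inputs.** With the normal approximation, n per arm = 2 × (z_alpha + z_power)² × (SD/difference)², where (175/50)² = 12.25.

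- Two-sided: 2 × (1.960 + 0.842)² × 12.25 = 192.3, so 193 per arm and **386 in total**. The t-test version gives 194 per arm, 388 in total.
- One-sided: 2 × (1.645 + 0.842)² × 12.25 = 151.5, so 152 per arm and **304 in total**.

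Neither reproduces 257. The two-sided shortfall is (386 − 257)/386 = 33%; the one-sided shortfall is (304 − 257)/304 = 15%.

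**2. Power with 257 in total (128.5 per arm).** The standardised difference is 50 / (175 × √(2/128.5)) = 2.290.

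- Two-sided: Φ(2.290 − 1.960) = 62.9% (62.6% with the t-test).
- One-sided: Φ(2.290 − 1.645) = 74.1%.

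**3. What would make 257 correct (two-sided)?** Either an SD of about 143 ml in place of 175, or a difference of about 61 ml in place of 50. Neither appears in the protocol. Allocation of 2:1 or 3:1 raises the total (435 and 516) and does not lower it.

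**4. Which sidedness did the authors use?** The second calculation in the same section gives a clue. For 18% against 9% at 80% power and 0.05, the arcsine formula is n per group = 2 × (z_alpha + z_power)² / h², with h = 2·arcsin√0.18 − 2·arcsin√0.09 = 0.876 − 0.609 = 0.267.

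- Two-sided: 2 × 7.849 / 0.267² = 220.3 (h carried unrounded), so 221 per group. This matches the protocol's figure.
- One-sided: 173.6 per group, which does not match.

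The section therefore appears to use a two-sided 0.05 for the binary outcome. The consistent answer for the mean is 386.

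**5. Power for 50 ml at the planned size (two-sided, SD 175).**

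| Women with a reading | Power |
|---|---|
| 486 | 88.3% |
| 442 | 85.2% |
| about 437 (486 less 10%) | 84.8% |

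The correct requirement of 386 lies below all three sizes.

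**The case against.** The strongest reply is that 257 drives nothing. Enrolment is set by the binary outcome (442, plus 10%, giving 486), and the inflation is said to serve both primary outcomes. No interim analysis, stopping rule or reduced-sample fallback refers to 257. To end with 257 readings, the trial would have to lose (486 − 257)/486 = 47% of its women. All of this stands, and it limits the consequence to the written justification. It does not make the figure right.

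A second reply is that the test may have been meant as one-sided. That softens the error but does not remove it, since 304 are then needed and 257 gives 74% power.

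A reader might infer three stronger things that the protocol does not support:

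- *That the trial is underpowered for mean blood loss.* It is not. On the protocol's own inputs, 486 women give more than the stated 80%.
- *That the closing sentence on sufficiency is also wrong.* It is true at 80% power, the only level that the section names. Adding the power figure would make it more informative, but its absence is not an error.
- *That the plan aimed for 90% power and misses it.* At 90% power, two-sided, the size per arm is 2 × (1.960 + 1.282)² × 12.25 = 257.4. A per-arm figure at 90% could thus have been reported as a total at 80%. This is a possible explanation and no more. The protocol never mentions 90% power, so falling short of the roughly 516 women it would need is not a defect.

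**Conclusion.** The point holds as a wrong figure in the sample size justification of a primary outcome. On the stated inputs, the total should be 386 two-sided (304 one-sided), and 257 gives about 63% power (74% one-sided). The two-sided values are the better reading because the 221 per group reproduces only with a two-sided test among the arcsine calculations shown. The result assumes a common SD of 175 ml, equal allocation and an unadjusted comparison of means. Design, enrolment and the claim that 486 suffices for 50 ml are unaffected. It is a correction of modest weight, worth making because the number is attached to the first primary outcome and is simple to put right.

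**What to change.** In Explanation of Sample Size:

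- Replace the total of 257 with: *386 in total (193 per arm), two-sided alpha 0.05, 80% power, assuming an SD of 175 ml in both arms*.
- Add the power to the closing statement: *486 women give about 88% power, or about 85% if 10% of readings are missing, to detect a 50 ml difference at an SD of 175 ml*.

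If the sponsor intended a one-sided test, the section should say so and give 304 in total.

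The cost is one corrected figure and one added power statement. The enrolment target stays at 486.

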**Description of Research**

This double-blind, controlled and randomized study will be carried out in a hospital where policy dictates that all women should receive 10 IU of prophylactic oxytocin in the third stage of labor. Furthermore, the majority of women who give birth in the study hospital already have an IV line in place. The study objective will be to evaluate the impact of route of administration of 10 IU oxytocin on postpartum bleeding. Eligible women who provide informed consent and give birth vaginally will be randomized to receive either:

- 10 IU oxytocin via IV infusion
- 10 IU oxytocin via IM injection

Oxytocin 10 IU will be administered either by IV infusion or IM according to randomization assignment as soon as possible after delivery of the baby. The IV infusion will be done by placing 10 IU of oxytocin in a bag of saline solution of 500 cc and then administered over 40 minutes (eg, 12cc/min or 240drops/min). All study participants will receive oxytocin by IV infusion or by IM injection, based on randomized allocation, and the corresponding placebo by the non-assigned route.

To avoid any potential bias that knowledge of the route of administration of oxytocin may have in the quantification of blood loss, study staff members and participants will not know the assignment of the route of administration of the active drug. Since all delivering women in the study hospital routinely have an IV line in place, all study participants will receive oxytocin by either IV infusion or IM injection, based on randomization assignment, in addition to placebo by the non-assigned route. Blood loss will be measured in a calibrated container for 1 hour. If a woman experiences excessive bleeding or PPH, she will receive treatment according to standard of care at the study site.

Independent of the diagnosis of PPH, consenting women who have a vaginal delivery will have their postpartum blood loss measured using a standardized receptacle, in addition to other indicators and outcomes recorded during the immediate postpartum period to assess the relationship between shock index and PPH outcomes. Blood loss will be measured for 1 hour, and if PPH diagnosed, measurement will continue until cessation of active bleeding. Pulse and blood pressure will be measured at pre-defined intervals (15, 30, 45, and 60 minutes) in order to document hemodynamic changes that occur during the immediate postpartum period.

***Eligibility Criteria***

*Inclusion criteria*

All women who present in active labor for a live birth at the study hospital will be considered for participation in the study. Women who present for care for a vaginal delivery will be enrolled. Independent of being diagnosed with PPH, among women who provide their consent and who have vaginal delivery, postpartum blood loss will be collected and measured, as well as other clinical measures recorded in the immediate postpartum period in order to evaluate the relationship between the shock index and outcomes of PPH.

*Exclusion criteria*

Women who are:

- Planned or transferred for delivery via Cesarean section
- That reject having an IV line in place
- Unable to provide informed consent due to mental impairment, distress during labor or other reason
- Unwilling and/or unable to respond to questionnaires about background characteristics.

If at any point in time the woman wants to withdraw from the study, she will be dismissed and data collection will cease.

